### Interventions

#### Experimental intervention

The intervention product for this pilot trial is a moisturising oil (commercially available moisturising oil) marketed to increase skin moisture. It contains an oil base: Paraffinum liquidum and Isopropyl Palmitate and parfum (Johnson’s baby oil).

Each woman randomised to the experimental intervention group will receive two plastic bottles of the moisturising oil with 200 mL in each. This is based on each woman applying ~ 2 mL per day (14 mL per week). Based on each woman applying the oil over 26 weeks, i.e. up until approx. 38 weeks of gestation (Fig. 1), each woman will require approximately 400 mL of oil in total. Each woman will be asked to apply ~ 2 mL to their abdominal skin daily after showering and before drying their skin. This will equate with two pumps of oil to ensure consistency in the amount applied.

Instructions for applying the oil will be printed on a label on the bottles as will the appropriate safety advice (see “Safety and undesirable effects” below). Women will be advised to apply the oil into their abdominal skin once daily from 12 weeks of gestation. They will be advised to apply the oil to their damp abdominal skin after showering and to ‘pad dry’ the area. The researcher will instruct them in the application of the oil. Women will be asked not to use any other skin product on their abdomen to maintain treatment fidelity and to complete a diary record of their daily application of the intervention oil and of any other product applied to their abdomen during the trial period (Fig. 1). They will also be asked to keep the empty oil bottles and bring them to the outcome assessment interview at 38–41 weeks.

#### Control intervention

Women allocated to the control group will not use any treatment and will be asked not to use any other skin product on their abdomen to maintain treatment fidelity. They will also be asked to keep a diary record (Fig. 1) and to document any product applied to their abdominal skin so that this can be assessed as part of the pilot trial.

All women will receive a two-weekly text to remind them about their participation in the trial and to complete the diary. A text message reminder will also be sent to women at 37 weeks to bring their empty oil bottles to the outcome assessment interview as appropriate.

#### Outcome measures

In order to evaluate the feasibility of conducting a definitive randomised controlled trial to evaluate the effectiveness of a moisturising oil (commercially available moisturising oil) compared to no treatment for the prevention and reduction in severity of striae gravidarum, the outcomes for this pilot study are:Number and proportion of women who are recruited, enrolled, complete the study and adhere to the intervention and control guidelines;Percentage of potentially eligible women who are recruited/enrolled to the study;Challenges with the randomisation process;Number and proportion of women who withdraw, drop out or deviate from the protocol guidelines;Reasons for non-recruitment, non-adherence or attrition;Women’s rating of the tolerability/acceptability and effectiveness of the intervention;Completeness of data collection for outcomes;Challenges with data analysis;Number and proportion of women developing striae gravidarum in the intervention and control groups;Number and proportion of women developing mild, moderate or severe striae gravidarum;Women’s perception of the severity of striae gravidarum (Fig. 1).

In addition to the above outcomes, birth data will also be collected following each birth from the labour ward register on birth gestation and infant weight (Fig. 1) and recorded on the outcomes assessment form.

#### Assessment of the development and severity of striae gravidarum

The development and severity of striae will be assessed using the Davey instrument [32] and the classification system of mild, moderate or severe as used by Soltanipour et al. [33]. It will entail dividing the abdomen into four quadrants and using an ordinal scoring scale to score each quadrant based on the number of striae present as above. However, the numbers in each quadrant will be interpreted as follows: 0 = no striae in a quadrant; 1 = striae do not affect a quadrant completely; and 2 = striae affect a quadrant completely [33]. Scores for each quadrant will be combined and graded as follows: women with a total of ‘0’ will be graded as having ‘none’, ‘1–3 mild striae, 4–6 as moderate striae, and 7–8 as severe striae’ [33]. The assessment will take place in a well-lit room with adequate natural day or artificial lighting and will be undertaken by the researcher or a research assistant.

#### Sample size and feasibility of sample size

A sample size of 228 women (114 per arm) is needed in the definitive trial to have 80% power to detect an absolute difference in the proportion of participants developing stretch marks of 0.20 [14] that is 0.47 [23] to 0.27 at the 5% significance level based on a two-sample test for a binomial proportion. This sample allows for 20% attrition. However, for the pilot trial it is proposed to recruit 20 women in each arm to assess the feasibility of running such a trial and to inform variable parameters. This sample size equates to 17.5% of the sample size needed for the main trial. The pilot data will be incorporated into the definitive trial, if feasible, as a seamless trial with an indicator variable used to distinguish pilot from non-pilot data. Furthermore, the attrition rate in the pilot trial will inform the final sample size for the main trial. This sample size is considered acceptable for a pilot study [34].

The pilot trial will involve one large maternity hospital with approximately 3000 births annually, which includes approximately 1100 first-time mothers. It is anticipated that circa 80 mothers will be booked per month and it will be feasible to recruit 40 first-time mothers over a three- to four-month period. This takes into consideration women who will refuse to participate and women who will not be eligible.

### Randomisation

#### Random sequence generation

The random allocation sequence will be generated using the random number generator (the Mersenne Twister) available in StatsDirect [35] by an independent person. Women will be allocated to the intervention and control group using a 1:1 randomisation ratio using random block sizes to ensure that the group to which each woman will be allocated will be determined by a chance process and cannot be predicted.

#### Allocation concealment mechanism

Allocation concealment will be ensured using sequentially numbered opaque envelopes prepared previously by a person independent from recruitment or allocation of participants to groups. Integrity of the process will be ensured by the researcher recording the woman’s name and the number of the next unopened envelope in the woman’s trial register form in the presence of another colleague and by both persons signing the unopened envelope. Following this, the envelope will be opened and the group allocation and study ID revealed [36]. Group allocation and study ID number which corresponds to the envelope number for that woman will be recorded on the trial register form.

### Blinding

#### Blinding of participants and personnel (performance bias)

Due to the technical design of the intervention, the women, the healthcare professionals caring for them and the researcher will not be blinded to which group the participant is randomised.

#### Blinding of outcomes assessment (detection bias)

As above, the outcome assessor will not be blinded to the group to which the participant is randomised.

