**Fig. 2 Fig2:**
[figure not shown]
Flow of participants through the trial

Women who agree to participate will be asked to sign three copies of the consent form and these will also be signed by the researcher. One copy will be returned to the woman, one will be put in the woman’s hospital records and the third will be kept for the research records. Women who are eligible and who decline to participate will be asked for their consent to disclose their reasons for non-participation. Further, women who subsequently decide to withdraw from the study will be asked to contact the researcher as outlined on the participant information leaflet**.** Women will then be asked by the researcher over the phone to give their consent to: (1) retention of data collected before their withdrawal from the study; or (2) retention of data collected before their withdrawal from the study and the inclusion of data collected routinely; or (3) that they wish to withdraw completely.

When written consent is obtained as outlined, the researcher will select the next sequentially numbered opaque envelope with the woman’s allocation. The researcher will then record the woman’s name and the envelope number in the woman’s trial register form in the presence of another colleague; they will both then sign the unopened envelope. Following this, the researcher will open the envelope revealing the group allocation and study ID, both of which will be recorded in the trial register form as above.

Women will complete a demographic and baseline characteristics’ data form as part of the case report form (CRF), which seeks information on name, date of birth, medical history, drug use, smoking status, maternal body mass index (BMI) at enrolment (BMI will also be assessed at 38–41 weeks of gestation at time of outcome assessment) and family history of first-degree relative developing striae in pregnancy.

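### The striae scorer is left unblinded for a reason that does not cover a separate assessor, although existing staff could score unaware of allocation

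*Protocol article*

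**What the plan says.** Under Blinding of participants and personnel, the protocol article gives the reason for an open trial: "Due to the technical design of the intervention, the women, the healthcare professionals caring for them and the researcher will not be blinded". The next section, on outcome assessment, refers back to that reason and adds only that "the outcome assessor will not be blinded to the group to which the participant is randomised".

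Under Assessment of the development and severity of striae gravidarum, each of four abdominal quadrants is scored 0 for no striae, and otherwise "1 = striae do not affect a quadrant completely; and 2 = striae affect a quadrant completely". The total of 0–8 is graded none, mild, moderate or severe. The assessment "will be undertaken by the researcher or a research assistant".

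Two other sections show who learns the allocation. Under Enrolment to the trial, "the researcher will open the envelope revealing the group allocation and study ID, both of which will be recorded in the trial register form". Under Experimental intervention, "The researcher will instruct them in the application of the oil". The same section asks oil-arm women to "keep the empty oil bottles and bring them to the outcome assessment interview". Participant follow-up collects adherence, tolerability and undesirable effects at the same visit as the striae score and sets no order.

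The sample size section plans to fold the pilot data into the definitive trial, if feasible, with a variable marking pilot records.

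**The concern.** The protocol separates performance bias from detection bias but justifies both with one reason. Comparing oil with no treatment makes it impossible to mask the women and whoever hands out and explains the oil. It does not by itself stop another person from looking at the abdomen near term without knowing the group.

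As written, the person who opened a woman's envelope and taught her to use the oil may also decide whether she has striae and whether a quadrant is partly or completely affected. Even a scorer who starts unaware could learn the group from the bottles or the adherence questions before scoring.

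There is no placebo, so expectation can act on the score in one direction. Whether striae develop is the basis of the definitive trial's sample size, and both their occurrence and their severity are in its null hypothesis. If pilot records enter that trial, any difference in scoring between arms enters with them. An indicator for pilot data separates pilot from later records; it does not correct a between-arm bias inside the pilot.

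**Working it through.** **1. Does the stated reason reach the scorer?** Setting the sections side by side:

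| Role | Must know the allocation? | Source |
|---|---|---|
| Women | Yes: they apply oil or nothing | Interventions |
| Healthcare professionals | Named as unblinded | Blinding of participants and personnel |
| Researcher | Yes: opens the envelope and teaches the oil | Enrolment; Experimental intervention |
| Research assistant as scorer | Nothing requires it | Assessment of striae |

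The assistant is already a permitted scorer. The assistant may, however, also recruit and take consent (Recruitment, Enrolment) and has access to the paper data (Data management). The assistant could also be the colleague who witnesses the envelope (Allocation concealment mechanism). So the assistant is not automatically unaware; those routes would have to be closed.

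**2. The plan's own sample size.** Inputs from the sample size section: 0.47 versus 0.27, two-sample test of proportions at 5%, 80% power, 20% attrition. I take the test as two-sided. The mean proportion is 0.37.

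n per arm = [1.96·√(2·0.37·0.63) + 0.8416·√(0.47·0.53 + 0.27·0.73)]² / 0.20² = (1.3382 + 0.5622)² / 0.04 = 90.3, so 91.

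With attrition, 91/0.8 = 113.75, so 114 per arm and 228 in total. The stated figure reproduces, and no sample size is disputed.

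**3. Illustration of the bias.** The misscoring rates are my assumptions; the documents give none. Suppose there is no true effect and 0.47 in both arms develop striae. The test is the pooled chi-square at the two-sided 5% level with 91 per arm, and rejection probabilities come from full enumeration. With no misscoring the rejection rate is 4.5%.

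*Unblinded scoring throughout the definitive trial, errors in both directions.* A share f of stria-free controls is scored as affected and a share f of affected oil users as clear.
- f = 10%: control 0.47 + 0.10·0.53 = 0.523; oil 0.47 − 0.10·0.47 = 0.423. The spurious difference is 0.10, half the 0.20 target. Rejection is 25.8%.
- f = 5%: 0.4965 versus 0.4465. Rejection is 9.6%.

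*Unblinded scoring throughout, errors in the oil arm only.*
- f = 10%: 0.47 versus 0.423, a difference of 0.047. Rejection is 9.2% (9.7% by normal approximation).

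*Errors in both directions, confined to the pilot's share.* The share is 20/114 = 17.5%.
- f = 10%: spurious difference 0.175·0.10 = 0.0175. Rejection is 5.1%.
- f = 5%: rejection is 4.7%.

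**The case against.** The protocol openly describes an unblinded, pragmatic pilot. It performs no hypothesis tests, and its progression criteria are recruitment, adherence and loss to follow-up. None of these uses the striae score. That stands, and it limits the point to the striae data.

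A reader might infer that the stated reason for not blinding concerns the participants alone. The text does not support that. It also names the carers and the researcher, and it fairly describes the researcher who randomises and instructs. What it does not cover is a separate scorer.

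A reader might also take 26% as the false-positive rate that this plan produces. That does not follow. The figure needs two-way misscoring at an assumed rate and unblinded scoring of every woman in the definitive trial. The description of a seamless trial may suggest the same scoring would continue, but the Methods also say that the pilot will help to modify the protocol for the larger study. If only the pilot is scored unblinded, the effect on the definitive test is small.

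Finally, masking may be imperfect. Women can disclose their group, and a perfumed oil applied daily to the skin being scored might leave scent or residue. The documents do not discuss this; it is an inference. It weakens the remedy but does not justify making no attempt.

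**Conclusion.** The point holds in a limited form. The protocol gives no reason that would prevent a separate person from scoring the abdomen unaware of allocation, and it already has a second staff member who is permitted to score. The striae score is observer-judged and is intended for use in the definitive trial, so it is worth protecting from the start.

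On assumed 10% misscoring with no true effect and 91 evaluable per arm, false positives range from about 5.1% (both directions, pilot share only) through about 9% (oil arm only, whole trial) to about 26% (both directions, whole trial), against 4.5% with none. The upper figures depend on the definitive trial keeping the same scoring. It would be wrong to conclude that the pilot's feasibility aims fail: recruitment, adherence and retention are little touched by who scores the striae. This is an inexpensive improvement that should be made, not a fatal flaw.

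**What to change.** Amend the sections on assessment of striae, allocation concealment, blinding of outcome assessment, enrolment and follow-up as follows.

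- The scorer is the research assistant, or whichever of the two existing staff neither opened nor witnessed that woman's envelope. The scorer has no access to her trial register form.
- Scoring is the first act of the visit, on a form that does not show the allocation. The woman is asked beforehand not to disclose her group.
- Bottles, diary, adherence, tolerability and undesirable-effect questions come afterwards.
- Where only one person can attend, striae are still scored before bottles and interview.
- At every visit, record whether the scorer knew the allocation. The pilot then shows how well masking works before the definitive trial relies on it.

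**Cost.** No extra staff, visits or sample size are needed. The new elements are a duty rota, a separate scoring form, a fixed visit order, a limit on access to the register and a request to the women, over at most 40 visits. Both staff must be present at some clinics, and masking may still fail in some women. The Trial status section reports that nobody had been enrolled at that protocol version, so the change could apply to every participant.

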#### Recruitment to the trial

Given that most first-time mothers will be eligible for inclusion in the study, an ethics committee-approved study information pack will accompany the booking appointment notification sent to each first-time mother by the clinic administrator. The study pack will include a letter inviting the woman to participate in the study and an information leaflet describing the background, purpose and study details. The information leaflet will provide contact details should potential participants have questions about any aspect of the study. This process ensures participants have time to decide whether they wish to participate and complies with best practice in obtaining consent [37].

The researcher will approach women as they wait for their booking appointment in the clinic while the support of midwives and obstetricians will be sought in identifying potentially eligible women. Thus, at each antenatal booking clinic during the recruitment phase, all primigravid women will be approached by the researcher or a research assistant and given the opportunity to discuss the study details before inviting them to participate in the study. A trial register form will be completed for each woman and each woman screened will be assigned a unique study ID number.

#### Enrolment to the trial

Women who are attending for their antenatal booking appointment and who are screened and deemed eligible and agree to join the study will be asked by the researcher or a research assistant to give written consent before randomisation (Fig. 2), including consent to receiving two-weekly reminder texts, which reminds participants to complete the daily study diary.

**Fig. 2 Fig2:**
[figure not shown]
Flow of participants through the trial

Women who agree to participate will be asked to sign three copies of the consent form and these will also be signed by the researcher. One copy will be returned to the woman, one will be put in the woman’s hospital records and the third will be kept for the research records. Women who are eligible and who decline to participate will be asked for their consent to disclose their reasons for non-participation. Further, women who subsequently decide to withdraw from the study will be asked to contact the researcher as outlined on the participant information leaflet**.** Women will then be asked by the researcher over the phone to give their consent to: (1) retention of data collected before their withdrawal from the study; or (2) retention of data collected before their withdrawal from the study and the inclusion of data collected routinely; or (3) that they wish to withdraw completely.

When written consent is obtained as outlined, the researcher will select the next sequentially numbered opaque envelope with the woman’s allocation. The researcher will then record the woman’s name and the envelope number in the woman’s trial register form in the presence of another colleague; they will both then sign the unopened envelope. Following this, the researcher will open the envelope revealing the group allocation and study ID, both of which will be recorded in the trial register form as above.

Women will complete a demographic and baseline characteristics’ data form as part of the case report form (CRF), which seeks information on name, date of birth, medical history, drug use, smoking status, maternal body mass index (BMI) at enrolment (BMI will also be assessed at 38–41 weeks of gestation at time of outcome assessment) and family history of first-degree relative developing striae in pregnancy.

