### Participant follow-up

Women will be followed up over a period of approximately 26 weeks, during which two-weekly reminder texts to complete the study diary will be sent. Outcome data will be collected at the antenatal clinic appointment at 38–41 weeks of gestation (Fig. 1).

Based on the clinic attendance lists, the researcher will arrange to meet each woman at one of their antenatal appointments at 38–41 weeks of gestation as above to undertake the outcome assessment. Women will be assessed for the development of striae and the severity of striae using the assessment instruments outlined above. In addition, the following data will be collected:Gestation at assessment;Current weight (to determine weight gain [% and absolute gain] during pregnancy);BMI;Mid-abdominal circumference;Development of polyhydramnios;Gestation at onset of striae as applicable;Development of striae in other body areas;Adherence to the intervention or control guidelines or not and reasons for same;Adverse event/undesirable effect (see below);Women’s evaluation of the tolerability and the effectiveness of the intervention;Women’s perceptions of the severity of striae gravidarum.

In addition, following the birth, the researcher will collect data on the following, from the labour ward register:Gestational week at birth;Weight of infant (Fig. 1).

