### Safety and undesirable effects

In keeping with the safety advice for the moisturising oil, women will be advised at recruitment that the oil is for external use only and should be kept out of the reach of children. They will be advised that in the event of a rash occurring or breathing problems or any other undesirable effect associated with the oil, that they discontinue the application of the oil and contact their general practitioner. They will also be asked to contact the researcher who will complete an undesirable effect form and the undesirable effect record log**.** The researcher will also complete a Cosmetic Product Undesirable Effect Report for the Health Products Regulatory Authority (HPRA) [38].

Adverse events for this study are classified as undesirable effects and serious undesirable effects [38] as follows:Undesirable effect – ‘…an adverse reaction to a cosmetic product under normal or foreseeable conditions of use’, (e.g. ‘…irritant and allergic effects, sensitivity to light and itching’;Serious undesirable effect – ‘…an undesirable effect which results in temporary or permanent functional incapacity, disability, hospitalization, congenital anomalies, an immediate vital risk or death’.

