### Criteria for proceeding to the main trial

The decision to proceed to the main trial will be made by the Trial Steering Committee based on the following criteria:≥ 40% of eligible women can be recruited;≥ 70% of women adhere to the intervention and control guidelines;<  20% of women lost to follow-up.

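### The withdrawal script has no option to stop the allocated guideline, diary or texts and still have the 38–41 week assessment, so some outcomes may be lost avoidably

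*Protocol article*

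**What the plan says.** The section Enrolment to the trial states that "women who subsequently decide to withdraw from the study will be asked to contact the researcher". She is then asked by phone to consent to one of three things:

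- "1) retention of data collected before their withdrawal from the study";
- option 2, "retention of data collected before their withdrawal from the study and the inclusion of data collected routinely";
- "3) that they wish to withdraw completely".

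The section on assessing striae says that the scoring "will be undertaken by the researcher or a research assistant", using a study instrument. Participant follow-up fixes the time: "Outcome data will be collected at the antenatal clinic appointment at 38–41 weeks of gestation". The woman's perception of severity and her rating of tolerability are collected at the same visit. The only items taken from the labour ward register are birth gestation and infant weight.

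The criteria for proceeding to the main trial include a limit of under 20% "of women lost to follow-up". The sample size section adds that pilot attrition will inform the main trial's size, and that pilot data will be carried into the main trial if feasible.

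**The concern.** The script goes straight from full participation to no further study contact. A woman may be tired of the diary or the texts, or no longer want to follow her allocated guideline, and yet have no objection to an examination at an antenatal visit. If she phones and her wish is handled as withdrawal, no option on the list lets her say so.

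The text makes this mix-up realistic in three ways:

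- A woman with an undesirable effect is told "that they discontinue the application of the oil and contact their general practitioner", and also to contact the researcher. That is the same contact used for withdrawal, and the article does not say there that she stays in follow-up.
- Women who decline to give up other creams are excluded at entry. A control woman who later starts a product may conclude that she no longer belongs in the study. The Background cites a survey in which 78.2% of pregnant women used a product.
- One listed outcome counts withdrawal, drop-out and deviation together.

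At stake are a progression criterion, a stated pilot objective (tolerability and acceptability), the attrition rate used to size the main trial, and by-arm striae proportions that may be carried forward.

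**Working it through.** **1. What each option leaves available.**

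| Item | Where it comes from | Option 1 | Option 2 | Option 3 |
|---|---|---|---|---|
| Data before withdrawal | case report form, diary | kept | kept | not offered |
| Birth gestation, infant weight | labour ward register | no | yes | no |
| Striae score | study staff, 38–41 weeks | no | no | no |
| Perceived severity, tolerability rating | outcome visit, 38–41 weeks | no | no | no |

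The entries for option 2 assume that routine records hold no quadrant striae score. The article names no routine source for one.

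**2. The plan's own sample size.** Inputs are 0.47 and 0.27, 80% power, a 5% level (taken as two-sided) and 20% attrition. The pooled formula is n = [1.960·√(2·0.37·0.63) + 0.842·√(0.47·0.53 + 0.27·0.73)]² / 0.20² = 90.3, so 91 per arm. Then 91/0.80 = 113.75, so 114 per arm and 228 in total. The stated figure is reproduced and is not in dispute. With 91 assessed per arm, power is 80.3%. The allowance therefore restores power only when loss is unrelated to the outcome.

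**3. Progression and main-trial size.** 20% of 40 is 8, so under 20% means at most 7 women (17.5%). As an illustration, suppose 8 are recorded as lost and 2 of them would have accepted the assessment.

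- As recorded: 8/40 = 20%, the criterion fails, and the main trial needs 91/0.80, so 114 per arm (228).
- With those two assessed: 6/40 = 15%, the criterion is met, and the main trial needs 91/0.85 = 107.06, so 108 per arm (216).

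The number two is an assumption. The arithmetic shows how little is needed.

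**4. Possible bias (assumed, not documented).** Let p be the true proportion with striae, L the overall loss, and r the ratio of loss in women with striae to loss in women without. Loss among women without striae is q = L/(p·r + 1 − p), and the observed proportion is p(1 − r·q)/(1 − L).

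Worked case with p = 0.47, L = 0.20, r = 2: q = 0.20/1.47 = 0.136, r·q = 0.272, and the observed proportion is 0.47·0.728/0.80 = 0.428.

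With L = 0.20 in both arms (about 91 assessed per arm) and a true difference of 0.20:

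| r | Control observed | Difference, dependence in control only | Power |
|---|---|---|---|
| 1 | 0.470 | 0.200 | 80% |
| 1.5 | 0.445 | 0.175 | 70% |
| 2 | 0.428 | 0.158 | 61% |
| 3 | 0.406 | 0.136 | 49% |

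Dependence in the oil arm only works the other way. At r = 2, q = 0.20/1.27 = 0.157, the observed oil proportion is 0.27·0.685/0.80 = 0.231, and the difference becomes 0.47 − 0.231 = 0.239. With the same r in both arms, the difference stays at 0.196–0.200 and power at 80–84%.

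**The case against.** The strongest reply is that the article does keep stopping the oil apart from leaving the study. The three options are for women who decide to withdraw. Participant follow-up has the researcher meet every woman at 38–41 weeks and record there whether she adhered and why. Intervention fidelity treats even fewer than 10 applications as an adherence category. The safety section does not call stopping the oil withdrawal, and use of other products is to be recorded in the diary. Adherence and loss to follow-up are separate progression criteria. All of this stands. A reader might infer that any woman who stops the oil, drops the diary or uses a product loses the striae outcome; the documents do not support that.

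A reader might also infer that such losses are likely to depend on striae and would bias the comparison substantially. Nothing in the article says so. A stark case can be built with no true effect: if 20% of one arm withdraw solely because striae appeared, that arm shows (0.47 − 0.20)/0.80 = 0.34, a spurious difference of 0.13. But this requires 0.20/0.47 = 43% of that arm's women with striae to leave and none of the others. The same loss in both arms gives a difference of zero. The plan's 20% is an allowance for attrition of any cause.

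Two further limits apply. In this pilot, which plans no hypothesis tests, striae is one of 11 outcomes, most of them about feasibility. And a woman who reports an undesirable effect leaves a record on its form, so information on tolerability is not wholly lost with her.

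What survives is narrow. The list of options is stated in the article, so this is not detail left to an unseen document, and nothing on it retains the assessment for a woman who would accept it.

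**Conclusion.** The point holds as a gap in a stated rule. A woman whose wish to stop is handled as study withdrawal is lost for the striae score, perceived severity and tolerability rating, although the assessment falls at an antenatal appointment. Non-adherent women who do not withdraw are unaffected.

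The firm consequences are for counting: at most 7 of 40 may be lost, and the pilot attrition rate feeds the main trial's size. Neither depends on why women leave, although how many would accept the added option is unknown. Bias in the by-arm proportions is conditional. It needs withdrawal to depend on striae differently between arms, and its direction depends on which arm is affected.

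The conclusion assumes that routine records hold no striae score. The information leaflet, consent form and full protocol are not shown and may address the boundary. This does not invalidate the pilot; it is an inexpensive improvement worth making.

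**What to change.** In Enrolment to the trial, put one option ahead of the present three: the woman stops the allocated guideline, the diary, the texts, or any of these, but still has the outcome assessment at 38–41 weeks. Keep the three existing options unchanged for women who want less contact or none.

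Count as withdrawn only women who decline the assessment. Report women who take the new option as non-adherent (or incompletely adherent, by the article's own grading), not as lost. Where they are non-adherent they then weigh on the 70% adherence criterion instead, so the change does not flatter the pilot. Women missed for other reasons remain lost to follow-up.

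The cost is one more option to explain by phone and a minor ethics amendment. The assessment already takes place at an antenatal appointment, so no extra visit is needed. Trial status reports no participant enrolled at the time of writing, so the change could precede any withdrawal. It leaves every rule about using or stopping the oil as it is.
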